## 6.2 Methods for minimizing bias

The components of the primary endpoint “occurrence of an intracranial hemorrhage” will be assessed by independent readers blinded to all clinical information. They will not be involved in the enrollment or treatment of any patient and will have no information on the distribution of patients (i.e. the number of patients with hemorrhage or without hemorrhage).

For this purpose, all scans will be reconstructed in a standardized manner first by the coordinating center to guarantee comparability between all scans. Fixed slice sizes and angels will be used for all scans. After reconstruction all scans will be pseudonymized and randomized. The order of the scans will differ for each rater. Furthermore, a time limit of 90 seconds will be used for the evaluation of the FDCT scans (only applicable to the binary decision hemorrhage yes/no) to ensure comparability to real-life conditions. No time-limit will be set for the MDCT scans as these are set as ground truth and therefore their diagnostic power will not be benchmarked.

### 6.2.1 Randomisation

Not applicable

### 6.2.2 Blinding procedures

Due to the nature of the procedure under investigation (diagnostic test) it is not possible, that study subjects, site investigators and care providers will be blinded. Furthermore, subjects are not randomized since all undergo the same procedures (cross-sectional design).

The main endpoint outcome parameter “occurrence of an intracranial hemorrhage” will be assessed by independent readers blinded to all clinical data. All scans will be reconstructed in a uniform matter and randomized prior to being assessed by the core-lab. Block randomization with variable block length will be used. The MDCT and FDCT scans will be read by different, independent readers. They will not have access to the results of other readers nor share any information about the clinical investigation with each other.

6.2.3 Other methods for minimising bias

1. Enrollment of patients will take place prior to the FDCT. Therefore, the enrolling physician could not know the appearance of the bleeding on the FDCT scan. This approach was chosen to rule out that enrolling physicians only include patients in which the FDCT scan is of high technical quality and the bleeding is well recognizable.

2. All readings will be documented on standardized forms.

## 6.3 Unblinding Procedures (Code break)

Not applicable

# 7. CLINICAL INVESTIGATION POPULATION

The clinical investigation will be conducted in Switzerland, Finland, France, Spain, and the USA. A preliminary list of all participating centers can be found in the appendix A.

## 7.1 Eligibility criteria

Subjects fulfilling all of the following inclusion criteria are eligible for the investigation:

- Informed Consent as documented by signature or fulfilling the criteria for emergency or deferral consent
- Patients with symptoms suggestive of ischemic stroke (NIHSS ≥ 7) or suggestive of haemorrhagic stroke with a cranial non-contrast MDCT and a feasible non-contrast syngo DynaCT Sine Spin within 4 hours
- Patient presenting within 24 hours of last seen well
- Patients presenting directly to the treating hospital (i.e. mothership patients) OR transfer patients with the indication for repeated imaging according to the standard operation procedures of the treating hospital*
- Age above 18 years
- Agreement of treating physician to perform non-contrast syngo DynaCT Sine Spin

The presence of any one of the following exclusion criteria will lead to the exclusion of the subject:

- Severe metal artifacts on initial MDCT imaging
- Planned invasive interventions between MDCT and FDCT scan
- Clinical deterioration between MDCT and FDCT scan (i.e. an increase of the NIHSS of more than 4 points)
- Evidence of an ongoing pregnancy prior to enrollment. A negative pregnancy test before enrollment is required for all women with child-bearing potential

*In case of transfer patients external MDCT images must be available at the PACS of the enrolling center prior to enrollment and the enrolling physician must ensure that the quality of these scans is sufficient for the assessment of the primary endpoint.

## 7.2 Recruitment and screening

Recruitment takes place in an emergency setting through usual care. No additional screening or examinations (except in women with child-bearing potential a pregnancy test) compared to normal clinical practice are necessary. The MDCT will be performed completely independently from the study.

All patients presenting to one of the participating sites with symptoms suggestive of acute stroke (i.e. NIHSS ≥7) or of an intracranial hemorrhage should be screened for this trial. In case of patients referred from other hospitals they are only considered for participation in this trial if they have an indication for repeated imaging according to local standards of care. For clarification repeated imaging can be done with FDCT, if external MDCT was of sufficient quality, is in the PACS of enrolling center, was within 4 hours of the anticipated FDCT, and the clinical presentation of the patient has not substantially changed (i.e., increase of NIHSS of more than 4 points). Patients will be recruited in the emergency or MDCT room. Primary responsibility for recruitment of patients will lie with the PI at each site.

Patients will not receive compensation for taking part in the trial.

## 7.3 Assignment to investigation groups

All included subjects will be assigned to the investigation group. There is no control group. All subjects undergo the same procedures.

## 7.4 Criteria for withdrawal / discontinuation of subjects

A trial patient or his/her next of kin/LAR can withdraw his/her consent to participate in the trial at any time and without any declaration of reason. In this case the data collected up to this time will be used for evaluation of the trial to not compromise the validity of the clinical trial or its results.^1^ After the final analysis the data will be anonymized. If a person who was included in a clinical trial in an emergency situation dies before it has been possible to obtain consent or refusal his/her data can only be used for analysis if there is a statement of wishes confirming the patients will to participate in clinical trials or if the consent is given by the next of kin of the patient,^1^ unless otherwise foreseen by national law. In case a person was included into the trial with the consent of an independent physician (due to his/her inability to give informed consent and the absence of a next of kin/LAR) and the patient refused to give informed consent after regaining the capacity to consent or his/her next of kin/LAR refuses to give informed consent (in case the patient did not regain the capacity to consent), all his/her data has to be erased.

# 8. CLINICAL INVESTIGATION INTERVENTION

## 8.1 Identity of the medical device under investigation

The following medical device will be used in the clinical investigation:

ARTIS icono biplane angiography system with syngo application software.

| Product/Trade Name: | Software version: | Model: | UDI-DI: |
| --- | --- | --- | --- |
| ARTIS icono biplane | VE21 or higher | 11327600 | 04056869063317 |
| syngo application software | VE21D or higher | 11327667 | 04056869124162 |

### 8.1.1 Experimental Intervention (medical device)

The experimental intervention is a non-contrast syngo DynaCT Sine Spin scan of the head. The scan duration is seven seconds and according to dose measurements the effective dose is up to 2.5 mSv.^3, 6^ It is a standard imaging protocol for visualization of the brain parenchyma and skull. It belongs to a bi-plane angiographic system the ARTIS Icono (Siemens Healthineers).

### 8.1.2 Control Intervention (standard/routine/comparator)

The control intervention is a non-contrast cranial MDCT scan. The system for the scan is left at the discretion of the site investigator. It is standard of care and done in all subjects irrespectively of their participation in the clinical investigation.

### 8.1.3 Labelling and Supply (re-supply)

This is a post-market device investigation with a CE-marked device. Therefore, labelling according to Art. 6.10 ISO14155 does not apply.

*See Appendix C- US Protocol Amendments

### 8.1.4 Storage Conditions

The medical device is permanently installed, and the required ambient conditions are considered for system installation. Key ambient conditions during system operation in the examination room, control- and equipment room include (see the ARTIS icono datasheet for further details):

• Temperature range: 15 °C – 30 °C

• Relative humidity: 20 – 75 % without condensation

• Max. temperature gradient: max. 5 °C/h

• Barometric pressure: 70 – 106 kPa

## 8.2 Discontinuation or modifications of the intervention

Because the clinical investigation intervention is a single intervention, discontinuation of the intervention is not an issue within this trial. Modifications of the intervention (i.e., changing the imaging protocol) is not permitted.

## 8.3 Compliance with clinical investigation intervention

Because the procedure under investigation is a single intervention there are no specific strategies to improve adherence to the protocol. Adherence will be monitored centrally, and deviation will be directly discussed with each trial site.

## 8.4 Data Collection and Follow-up for withdrawn subjects

As there are no follow-up visits planed there is no foreseeable scenario in which a patient might be lost to follow-up.

## 8.5 Clinical investigation specific preventive measures

All site PIs will be trained by the Sponsor-PI or the American chair in the conductance of the examined imaging protocol. Site Pis have to ensure that all personal performing the examination at their site is properly trained in executing it. Dose measurements were performed before in cooperation with Siemens Healthineers to ensure that the radiation of the used protocol does not exceed 2.5 mSv.^6^

## 8.6 Concomitant Interventions (treatments)

Not applicable.

## 8.7 Medical Device Accountability

Medical Device Accountability does not apply since the devices are permanently installed. The model and serial number of the systems will be recorded for each investigational site, also in case of a system exchange.

## 8.8 Return, Analysis or Destruction of the Medical Device

Since the medical device is CE-marked and permanently installed, the return of the system does not apply. In case of device deficiencies, including malfunction, usability issues, or inadequacy in the information supplied by the manufacturer including labelling, either on-site service or remote service is performed. In case of exchange of defective parts, these will be returned to the manufacturer for analysis as part of the complaint handling process.

# 9. CLINICAL INVESTIGATION ASSESSMENTS

## 9.1 Clinical investigation flow chart/ table of clinical investigation procedures and assessments

[figure not shown]

The Schedule of assessments to be performed at each study visit is listed in the table below

| **Schedule of assessments** | | | |
| --- | --- | --- | --- |
| **Visits** | | **0** | **1** |
|  |  | **Screening and enrollment** | **Intervention** |
| **Assessment** | **Time Window** | 0 | 0 – 4 hours after Non-contrast MDCT scan |
|  | **Method** | Clinical Visit | Intervention |
| Informed consent | | X^1^ |  |
| Patient demographics (i.e. age, gender, pre-existing conditions) | | X |  |
| National Institute of Health Stroke Scale | | X |  |
| Pregnancy test (only in women of childbearing potential) | | X |  |
| Patient logistics (i.e. time from onset to admission / imaging) | | X |  |
| Medical history (including medication) | | X |  |
| Non-contrast MDCT head scan^2^ | | X |  |
| Enrollment | | X |  |
| Non-contrast syngo DynaCT Sine Spin FDCT head scan | |  | X |
| AEs | | Only if procedure related up to 24 hours after procedure | |
| SAEs | | Only if procedure related up to 24 hours after procedure | |

1. Post-hoc consent if patient was not able to give consent at trial inclusion (according to national and applicable law)

2. For clarification the MDCT scan could have been done in an external hospital (in case of transfer patients) if the images of the MDCT are available at the PACS of the enrolling hospital and the quality was deemed to be sufficient by the enrolling physician and all other in- and exclusion criteria are met

AEs Adverse events, FDCT Flat-detector CT, MDCT Multi-detector CT, SAEs Serious adverse events

## 9.2 Assessments of outcomes

All outcomes will be assessed by a blinded and independent imaging core-lab. For this purpose, all scans will be anonymized, reconstructed in a standardized matter (i.e. fixed slice thickness 5 mm, distance 3 mm and angles - orbitomeatal) and randomized prior to evaluation.

The main core-lab will be provided by the Neurovascular Imaging Research Core at UCLA ([name], University of California Los Angeles, Los Angeles, California, USA). The experience of the Neurovascular Imaging Research Core at UCLA as an imaging and angiography core lab is unrivaled, including more than 15,000 acute ischemic stroke cases treated with endovascular therapies in the last several years.

To ensure compliance with the Protocol and adequate acquisition technique of the FDCT and MDCT at the respective site the first five cases from each site will be deemed as lead-in cases. Cases can be excluded and deemed as Screen Failures if they show clear evidence of (a) operator failure (for example due to clear artifacts due to objects in the field of view, wrong positioning of head, wrong acquisition protocol, severe motion artifacts, missing reconstructions) or (b) technical failure due to missing calibration of the scanner. The ultimate decision to exclude cases is made by the Independent Core Lab (under the supervision of [name]). In such a case it is the obligation of the Sponsor to perform retraining. Excluded cases will be replaced to ensure adequate power.

The imaging core-lab will use a standardized form to note all endpoints, in specific:

- Primary outcome:
  - Occurrence of an intracranial hemorrhage (yes/no)

The primary outcome will be assessed on both scans.

Only on the MDCT scans the following variables will be assessed as well:

- - Type of intracranial hemorrhage (SAH, intraparenchymal hemorrhage, intraventricular hemorrhage, subdural hemorrhage, epidural hemorrhage)
  - Is the intracranial hemorrhage isolated to the infratentorial region? (yes/no)

Only on the FDCT scans the following variables will be assessed as well:

- - Was contrast-media present at the evaluation of the scan? (yes/no)
  - If yes, did it enhance your capability to detect/exclude a hemorrhage? (yes/no)

The MDCT scans will be read by one clinical and one core-lab reader. If the reading of the core-lab reader and the clinical reader are consistent this will be defined as ground truth. In case of inconsistencies, a second core-lab (provided by [name], Inselspital Bern) will be involved to define the ground truth (majority vote). Please refer to 6.1 for detailed information on the definition of ground truth.

All FDCT scans will be read by six readers. These readers will read all non-contrast syngo DynaCT Sine Spin scans independent from each other and share no information. They will be chosen in a way that it is secured that they do not work together or were trained together. None of the readers has seen the corresponding MDCT scans of the patient. In case most of the readers rate (at least 5 out of 6) an FDCT scan hemorrhage positive in a patient in whom the ground truth is hemorrhage negative, a second core-lab (provided by [name], Inselspital Bern) will be involved. This core-lab will be unblinded to all clinical information and determine if the bleeding occurred between both scans. In this case the patient will be excluded from the analysis.

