## 11.5 Planned Analyses

### 11.5.1 Dataset to be analysed, analysis populations

For the analysis the full analysis set (FAS) will be used. The FAS contains all patients for which the six readers read all non-contrast syngo DynaCT Sine Spin images and rated them on a two-point scale (presence or absence of hemorrhage).

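### Enrolled, scanned patients can be removed after FDCT for technical failure (including motion) or for one missing reading, with no stated timing or blinding, so FDCT failures can leave the only analysis set

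*Protocol*

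**What the plan says.** Patients are enrolled before the FDCT (Protocol 6.2.3 and 9.3.2). Section 9.2, repeated in the synopsis under measurements and procedures, describes a quality step. It opens with the statement that "the first five cases from each site will be deemed as lead-in cases" and continues: "Cases can be excluded and deemed as Screen Failures if they show clear evidence of (a) operator failure". Examples of operator failure include foreign objects causing artefacts and "wrong positioning of head, wrong acquisition protocol, severe motion artifacts, missing reconstructions". The second ground is a scanner that was not calibrated. On who decides: "The ultimate decision to exclude cases is made by the Independent Core Lab". On what follows: "Excluded cases will be replaced to ensure adequate power". The stated purpose covers acquisition of both FDCT and MDCT, and the sponsor must retrain the site.

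Section 11.5.1 defines the analysis set: "The FAS contains all patients for which the six readers read all non-contrast syngo DynaCT Sine Spin images and rated them", on a yes/no scale. Section 11.6 bases all analyses on that set and imputes nothing. Section 11.5.2 fits a logit model with random effects for reader and patient.

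Section 6.2.3 explains why enrolment comes before the FDCT: "This approach was chosen to rule out that enrolling physicians only include patients in which the FDCT scan is of high technical quality".

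**The concern.** A patient who has been enrolled and has had the FDCT is past screening. Removing that patient because the FDCT failed removes a result of the test under study.

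Some listed causes, such as a wrong protocol or an uncalibrated scanner, are plausibly site learning and unrelated to the patient. Severe motion is different. The population has NIHSS of at least 7 or suspected haemorrhage, and Section 9.3.1 advises against intubation between the scans. Motion can therefore belong to the patients in whom FDCT would be used for triage.

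Three safeguards are not written down:
- The exclusion sentence is not limited to the lead-in cases named just before it.
- Nothing places the decision before the haemorrhage readings.
- Nothing blinds the decision to the MDCT result, and the same core lab reads both modalities.

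The FAS definition is a second filter. Taken literally, a single missing rating removes the patient from every analysis. No analysis in the protocol counts a failed or incompletely rated scan against FDCT. At stake is whether sensitivity and specificity describe patients sent to FDCT or only those whose scan passed technical review and was fully rated.

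**Working it through.** **Plan's own figure.** Section 11.2 gives 238 patients before a 5% drop-out allowance and 252 after it. 238 / 0.95 = 250.5, so 251, or 252 with equal groups of 126. The figure reproduces. The allowance is 252 − 238 = 14, or 7 per group. The 90% power behind 238 cannot be reproduced, because the correlation between readers is described only as high.

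**Inputs.** Planned sensitivity 99% and specificity 98%, difficult-case sensitivity 70% with total weight 2%, margin 95% (Section 11.2); 126 positive and 126 negative patients; up to 30 sites (synopsis). The number k of excluded scans is an assumption, because the protocol gives no failure rate.

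**How many failures matter.** With k failed scans among n, and failed scans read correctly with probability q:

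accuracy = p × (n − k)/n + q × k/n

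Failed scans counted as incorrect (q = 0):
- Specificity: 95% is reached at a failed share of 1 − 0.95/0.98 = 3.1%, or 3.9 of 126. For k = 3: 0.98 × 123/126 = 95.7%. For k = 4: 0.98 × 122/126 = 94.9%.
- Sensitivity: 95% is reached at 1 − 0.95/0.99 = 4.0%, or 5.1 of 126. For k = 5: 0.99 × 121/126 = 95.1%. For k = 6: 0.99 × 120/126 = 94.3%.

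Failed scans read at chance (q = 0.5):
- Specificity, k = 8: 0.98 × 118/126 + 0.5 × 8/126 = 95.0% (0.9495), just below the margin.
- Sensitivity, k = 10: 0.99 × 116/126 + 0.5 × 10/126 = 95.1%. For k = 11: 94.7%.

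Replacement barely changes this. If 126 good scans are kept and the failures are added back as incorrect, specificity with 4 is 0.98 × 126/130 = 94.98%, and sensitivity with 6 is 0.99 × 126/132 = 94.5%.

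These sensitivity figures are unweighted. If 99% is read as the rate outside the 14 difficult cases, weighted sensitivity is 0.98 × 0.99 + 0.02 × 0.70 = 98.4%. Four failures among the other 112 positives then give 0.98 × 0.99 × 108/112 + 0.014 = 0.94955. A failure among the 14 difficult cases costs only 0.02 × 0.70/14 = 0.1 points.

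All of these are simple proportions, not the model intercept. Success also requires the lower confidence bound, not the point estimate, to exceed 95%, so fewer failures could change the result.

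**Reach of the rule.** If it covers lead-in cases only, at most 30 × 5 = 150 of 252 patients (60%) come under review. This is a ceiling on cases examined at the maximum number of sites, not an estimate of exclusions.

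**FAS.** A model with random reader and patient effects does not need six ratings per patient. Requiring all six is not needed to fit the model in Section 11.5.2.

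**The case against.** The strongest defence is that this is an ordinary lead-in. Separating a site's learning curve from device performance is a recognised choice. The rule asks for clear evidence, lists technical grounds, does not use haemorrhage visibility, and triggers retraining. The decision lies with an independent core lab that receives de-identified images (Section 1.8). A core-lab manual finalised before any reading may fix the timing, and the SAP may deal with the occasional missing rating. Much of this stands, and it rules out several stronger readings.

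- A reader might infer that accuracy is measured only on good scans. The text does not support that. Scans that are poor for reasons other than clear operator or calibration failure stay in, and the yes/no scale with no non-diagnostic option appears to force a reading on them.
- A reader might infer that all exclusions favour FDCT. The rule also covers MDCT, and removing an unreliable reference scan need not favour FDCT.
- A reader might take Section 6.2.3 as flatly contradicted. It concerns selection by enrolling physicians, whereas here a core lab decides on technical grounds. This is a tension with its aim, not a contradiction.
- A reader might assume that unreadable scans, or readings beyond 90 seconds, become missing. The protocol says neither, and it expects every reader to rate every scan.

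The defence does not supply the missing limits. The exclusion rule, replacement and FAS are fixed in this protocol, and a later sensitivity analysis would not change the primary population. Calling severe motion operator failure is also a choice made here.

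**Conclusion.** The point holds in a limited form. As written, the rules can remove FDCT failures from the only analysis set, after enrolment and scanning, without a stated limit to lead-in cases, a stated time before the readings, or blinding to the MDCT result. The all-six-readers condition can remove more patients without need. For FDCT failures the expected direction is upward, towards the non-inferiority conclusion.

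The size is unknown. The counts of about 4 of 126 negatives or 6 of 126 positives rest on the planned 99% and 98%, on unweighted proportions, and on scoring every excluded scan as wrong, which is the harshest convention. Read at chance, 8 and 11 are needed. They show that small numbers matter at this margin; they do not predict how many scans will fail.

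**What to change.** 1. In Section 9.2 and the synopsis, confine exclusion to the lead-in cases and to causes that do not come from the patient, such as wrong protocol, missing reconstruction or missing calibration. Require the decision before any haemorrhage reading, blind to the MDCT result and the ground truth. Take patient motion out of operator failure.
2. In Section 11.5.1, define the FAS as all other enrolled patients with an FDCT and a ground truth, using every available rating.
3. Report the number of excluded or non-diagnostic scans and the reasons, by bucket and by modality. Add a sensitivity analysis of all scanned patients, including replaced cases, with failed or unrated FDCT readings counted as incorrect. Scoring them this way in the primary analysis is a debatable convention and is not needed here.

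The cost is wording in the protocol and the core-lab manual plus one further analysis; for scanned patients the images already exist. Accuracy estimates may be slightly lower.
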